##### Secondary outcomes

The additional effect of the EbMG will be evaluated similarly to the primary outcome under consideration of group A versus group B. Since the sample size is calculated with regard to the primary outcome, these analyses are only exploratory.

For further secondary outcomes, PCPs who adhered to the protocol will be encompassed in the analyses. Adherence refers to the intervention groups and whether each PCP has submitted a minimum of at least four videos. To explore differences in the antibiotic prescribing rate at *t*_1_ depending on the communication skills of the PCPs in group A and B, linear regression analyses will be conducted.

Quantitative data from the evaluation questionnaire will be presented descriptively only.

For all analyses, 95 % confidence intervals will be calculated where applicable.

### Additional analyses

Depending on the scale level and the distribution, parametric or non-parametric methods (e.g. Chi-squared test, *t* test or Mann-Whitney *U* test) will be applied to ascertain whether differences exist between intervention groups (A + B) and the control group at baseline.

### Ethics

PCPs and their filmed patients will participate voluntarily and may withdraw from participation at any time without giving reasons. No data monitoring committee is necessary because of the known minimal to negligible risks of the intervention. No adverse events are to be expected in this kind of study. However, participants (PCPs) and the filmed patients can contact the study team with further enquiries.

Due to the fact that prescribing data is pseudonymised by an external position of trust at ZI and the diagnoses are transferred in compliance with the legal requirements of the national data protectionist, no data can be reduced to a specific person.

Moreover, values which will be interpreted in the analyses are an aggregate function of pseudonymised prescription data in terms of the patient. The reference to the individual patient is no longer possible and this is in line with this part of data protection. The second and sufficient part of data protection, which refers to the misuse of routinely collected data in the research project, will be ensured with the help of a statutory application at the Independent Centre for Data Protection SH (ULD), which is in frame for such cases.

The study was approved by the ethics committee of Luebeck University before the recruitment of participants on 9 June 2015 (number of approval: 15-139).

## Discussion

The MAAS-Global-D instrument, which measures communicative and medical skills, has recently been translated into German [22] and will be tested in a randomised controlled trial in primary care in Germany for the first time. The trial design (three arms: multiple interventional elements and comparison with a control group) contributes to an insight into the effectiveness of the different components to reduce antibiotic prescribing, which will also be supported by extensive evaluation. Thereby, barriers and enablers to implement parts of or the whole of the communication training on a large scale will be worked out. The choice of active clinician education procedures and further educational material for the PCP, such as EbMG, would appear to be promising intervention strategies [15, 16].

### Strengths and limitations of the study

The randomisation will ensure a random distribution of characteristics and probably create nearly equal groups. Due to the number of participants, a prior stratification would not be reasonable. A limitation of the study is that randomisation must be carried out at practice level because the routine data cannot be assigned to the individual PCP in group practices. Therefore, untrained PCPs in group practices might bias the effect of the intervention.

Using the PCPs’ routine data instead of self-documentation bears the advantage that the data is not subject to selection bias: for example, if a PCP does not include all cases with the defined diagnoses in their documentation or if patients deny being in the study. Also, recall bias or effects due to the interviewer can be excluded. The Hawthorne effect is probably smaller, too, as the PCPs’ attention is not constantly drawn to patients with the relevant diagnoses. The routine data further allows the possibility of including several years as *t*_*0*_, which can balance extremes due to different seasonal variations. Extremes in *t*_1_ cannot be balanced, but a rise in antibiotic prescriptions due to a growth in infections in this time period would equally affect intervention and control groups.

Routine data is, at the same time, secondary data with known limitations: an often poorer data quality caused, for example, by misclassifications goes along with no possibility of external validation (e.g. of diagnoses) in our subsample. Further weaknesses are the lack of information on prescriptions that were not redeemed and using data covering only those patients who have statutory health insurance. Due to the data format, we do not have any further information about the ongoing of a patient’s disease, e.g. whether patients who did not use antibiotics suffer from complications afterwards. Information about side effects of antibiotics is also not available. However, these important issues will be part of the process evaluation.

Sample size calculation for this study was difficult because not only the effect size but also the *t*_0_ prescribing rate of antibiotics for the three diagnoses in Germany are based on estimates. Additionally, as in many trials, we will also be confronted with the self-selection bias of PCPs. Those interested or already sensitised for the issues (antibiotic prescription, communication skills) are more likely to participate in our study.

However, if our hypothesis is not rejected, the communication training is an easy and cost-effective way to reduce antibiotic prescribing for PCPs in Germany, who are facing symptoms of respiratory infections on a daily basis and need to make decisions about treatment.

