## Methods/Design

### Trial design

The trial is designed as a randomised, controlled trial postulating superiority of the interventions over conventional care in family practices. The study consists of three arms and a primary endpoint of antibiotic prescribing rates of PCPs for acute bronchitis, sinusitis and pharyngitis over a 3-month period starting around 1 month after the communication training and education in the usage of EbMG. Randomisation of either of the two intervention groups or the control group will be performed at practice level with a 1:1:1 allocation. Therefore, random permuted blocks will be generated. Due to the data format, practices with more than one physician represent one case. The person assigning the participants to the groups will do so blinded. Further blinding does not fit the trial design.

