### Sample size

#### Primary outcome: evaluation of antibiotic prescribing rate in intervention groups compared to control group

Previous research has established that communication training can lead to a reduction of 12 % (95 % confidence interval −18.9 to −4.0) in antibiotic prescribing [17], with a mean of −4 % (standard deviation (SD) 15.6) in the intervention group and +8 % (SD 19.2) in the control group, respectively, from *t*_0_ to *t*_1_.

Additional definitions for sample size calculations are a power of 80 % and *α* = 5 %. A *t* test for unequal group sizes (Satterthwaite’s *t* test) results in 28 PCPs per study arm. Including an estimated dropout of 10 %, the total is 93 participants, yielding 31 per study arm.

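### Trial size is a poor reason to reject all stratification: one factor known at consent, practice type, could be balanced at almost no cost, for a modest gain in precision and credibility

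*Protocol article*

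**What the plan says.** Under Trial design, randomisation "will be performed at practice level with a 1:1:1 allocation", and "random permuted blocks will be generated". No stratification factor is named. The same section says that "practices with more than one physician represent one case".

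Under Strengths and limitations of the study, the authors expect that chance alone will "probably create nearly equal groups". They then dismiss strata: "Due to the number of participants, a prior stratification would not be reasonable". No other reason is given.

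Under Sample size, "the total is 93 participants, yielding 31 per study arm". Under Outcomes and Analysis, the primary comparison is the change in prescribing rate from t0 to t1, A+B against C, by a t test with no covariate named. Practice type, location, specialisation, t0 rate and patient numbers appear as covariates only in the secondary regression on the MAAS-Global-D score.

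**The concern.** Chance imbalance is larger in small trials, so a small number of units is normally a reason to restrict randomisation on one or two important factors. It becomes a reason against stratifying only when the strata would be too many and too sparse. The article draws no such line and rejects stratification altogether.

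Practice type is the obvious candidate. The eligibility criteria require every colleague in a group practice to consent, so it is settled before allocation. The authors themselves single out group practices as a limitation and list practice type as a covariate elsewhere. As described, neither the allocation nor the primary test uses it. What is at stake is some precision, and how convincing the comparison looks if the baseline table shows a visible gap.

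**Working it through.** **1. The plan's own sample size.** Inputs from Sample size: difference 12 points, SDs 15.6 and 19.2, power 80 %, alpha 5 % (taken as two-sided). A Satterthwaite t test with 56 versus 28 units gives 80.1 % power, and 54 versus 27 gives 78.6 %. So 28 per arm reproduces. For dropout, 84 x 1.1 = 92.4, rounded up to 93. The primary comparison is therefore 62 (A+B) against 31 (C).

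**2. Chance of a gap in practice type without strata.** Let K of the 93 units be shared practices and k of them fall in C. The gap in shares is

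k/31 - (K - k)/62 = (3k - K)/62.

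It reaches 10 points when |3k - K| is at least 6.2. With K = 37 (about 40 %), 12.3 are expected in C, and the threshold is met when k is 10 or fewer, or 15 or more. Summing the hypergeometric probabilities (93 units, 31 in C):

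| Shared practices (assumed) | K | P(gap at least 10 points) |
|---|---|---|
| 10 % | 9 | 0.06 |
| 20 % | 19 | 0.28 |
| 25 % | 23 | 0.31 |
| 30 % | 28 | 0.34 |
| 40 % | 37 | 0.37 |
| 50 % | 46 | 0.38 |

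For 30-50 % shared, the chance of a gap of at least 15 points is 0.15-0.19. A simulation of unstratified permuted blocks of 3 and 6, with each unit shared at random with probability 0.3 or 0.5, gave 0.30-0.37 for the 10-point threshold. Blocks alone therefore do not remove the problem.

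The figure 93 counts participants, while the randomised unit is the practice. If there were only 69 units (assumed, with about 33-50 % shared), the chance would be 0.43-0.45.

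**3. The same with strata.** With blocks of 3 inside each practice type, the number of shared practices in C can differ from K/3 by less than one. For K = 37 there are 12 full blocks and one further unit, so k is 12 or 13. With 31 units in C the gap is (36 - 37)/62 = -1.6 points or (39 - 37)/62 = +3.2 points. Even four strata (two binary factors, 93/4 = about 23 units each when both are at 50 %) remain workable: in simulation the chance of a 10-point gap fell to 0.02 % or less per factor, and C kept 28-34 units.

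**4. What imbalance in the t0 rate costs.** With the planning SDs, the standard error of the difference in change is

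sqrt(15.6²/62 + 19.2²/31) = sqrt(3.93 + 11.89) = sqrt(15.82) = 3.98 points.

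Assume an SD of 15 points for t0 and a slope of change on t0 of -0.4; the article gives neither. The chance difference in mean t0 then has SD 15 x sqrt(1/62 + 1/31) = 3.3 points. Through the slope it moves the difference in change by 0.4 x 3.3 = 1.3 points (one SD). That variation is already part of the 3.98. Removing it gives sqrt(15.82 - 1.74) = 3.75, a reduction of about 6 %.

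**The case against.** Much can be said for the plan, and most of it stands.

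- **The balance statement is not refuted.** A reader might infer that the expectation of nearly equal groups is false. The article says only that this will probably happen, and at 30-50 % shared practices a gap under 10 points has a 62-66 % chance. The 10-point threshold is also a reviewer's choice: moving one practice between A+B and C shifts the gap by 3/62 = 4.8 points.
- **Baseline imbalance does not pass straight into the estimate.** A reader might infer this from the unadjusted t test. But the outcome is t1 minus t0, so the baseline level is subtracted and only regression to the mean remains. The 1.3 points is part of the standard error and must not be added to it.
- **Untrained colleagues are a different problem.** They dilute the effect inside A+B, while controls receive no intervention. A 10-point gap puts A+B only 10 x 31/93 = 3.3 points from the overall share. If dilution cost 6 of the 12 points in shared practices (assumed), the estimate would move by about 0.033 x 6 = 0.2 points. The article nowhere says that practice type predicts change in the control group.
- **Not every factor is shown to be available.** The t0 quarters end in June 2015, but access to linked data depends on data-protection approval and on the KVSH extract, so availability at randomisation is not established.
- **Sparse strata are a real worry.** Three binary factors give eight strata of about 12 units, or about four per arm. Unstratified permuted blocks are valid, baseline differences will be examined, and A versus B is declared exploratory. An analysis plan not shown may add adjusted analyses.

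What does not stand is the reason given. None of these arguments makes trial size an obstacle to two strata on a factor already recorded at consent.

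**Conclusion.** The stated rationale is weak, and the point is of low severity. Size argues against many strata only. If 25-50 % of practices are shared, the unstratified plan carries a 31-38 % chance of a gap of 10 points or more in practice type between A+B and C. The chance is 28 % at 20 % prevalence and about 6 % at 10 %. The prevalence is an assumption.

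The primary test remains unbiased and its type I error is intact. The loss is in precision, about 6 % of the standard error for the t0 rate under the assumed SD and slope, and in credibility should a visible imbalance arise. The documents give no figure from which the precision gain for practice type itself could be computed.

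**What to change.** Replace the sentence rejecting stratification with:

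> Randomisation is stratified by practice type (single or shared) in permuted blocks; the primary model for the difference in change includes practice type and the t0 rate as covariates.

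The stratification factor belongs in the model so that the analysis matches the allocation. Stratifying on the t0 rate is optional: its availability before randomisation is not shown, and adjusting for it recovers most of that gain.

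The article appeared in April 2016, the first month of the post-intervention quarter, so randomisation may already be over. In that case withdraw the stated reason and prespecify the covariate adjustment before outcome data are seen.

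The cost is two randomisation lists instead of one and a regression model instead of a t test. No additional data are needed: practice type is known from consent, and the t0 rate is already required for the outcome.

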### Trial status

The trial has been registered in the German Clinical Trial Register (DRKS00009566) and is currently recruiting participants

## Abbreviations

EbMG: Evidence-based Medicine – Guidelines
KV: Association of Statutory Health Insurance Physicians
KVSH: Association of Statutory Health Insurance Physicians Schleswig-Holstein
*t*_0_: baseline: pre-intervention time period (quarter II in years 2013–2015)
*t*_1_: post-intervention time period (quarter II in 2016)
PCP: primary care physician
SH: Schleswig-Holstein, federal state in northern Germany
ULD: Independent Centre for Data Protection SH (Unabhaengiges Landeszentrum fuer Datenschutz)
ZI: Central Research Institute of Ambulatory Health Care in Germany
